### Outcomes

The primary outcomes of this trial consist of three parts: 1) Mean number of motivated alters who have photo-verified self-testing per index in each arm; 2) Proportion of first-time HIV testing among alters in each arm; 3) Proportion of alters with a positive HIV testing result in each arm.

The secondary outcomes of this study consist of three parts 1) Risky sexual behavior among indexes and alters in each arm; 2) Adverse events reported during secondary distribution among indexes and alters in each arm; 3) Attitude towards and past experiences of HIVST and sexual behavior among alters in each arm.

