## Methods/design

### Study setting and recruitment

This trial, conducted in Zhuhai, is a collaboration among the Social Entrepreneurship to Spur Health (SESH) research team, Zhuhai Center of Diseases Control (CDC), and Zhuhai Xutong Voluntary Services Center (hereafter, Xutong). Zhuhai, located in Southern China, has approximately 17,000 MSM with an HIV prevalence rate of 7% [12]. Xutong is a local gay community-based organization (CBO) founded in 2015 and has developed a digital network-based platform for individuals (all-over time) to apply for free HIV/syphilis self-testing kits provided by Zhuhai CDC. With Xutong’s social impact within the gay community, its volunteers will help with study recruitment, and their online platform will be used to support our intervention implementation.

Study recruitment advertisement will be posted via Xutong’s official account on WeChat, a popular social site in China similar to Facebook and Twitter. The recruitment information will also be advertised on BlueD, the largest social network app within the gay community in China. Potential participants can join the trial via the study ads and sign up for Xutong’s online platform.

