### Sample size

According to preliminary study results, on average, the number of alters motivated by an index man was 0.65 through standard secondary distribution, 1.0 through SD/monetary incentives intervention, and 1.4 through SD/monetary incentives plus peer referral intervention. We assumed that the variances of the three groups were equal with the same standard deviation of 0.5 (preliminary data, unpublished results). Further, we estimated an effective sample size of 300 participants (100 in each group), with a power of 0.90, an alpha of 0.05, and a lost to follow-up rate of 0.20.

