#### Primary analysis

We will first calculate primary outcomes in each arm, i.e., mean number of alters that each index recruited, proportion of first-time HIV testers, and proportion of alter testers with an HIV-positive result. Secondly, we will compare calculated means using two-sample t-test, and proportions using chi-square between SD/monetary incentives arm and control arm, SD/monetary incentives plus peer referral arm and control arm, and also between two intervention arms.

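### Three unranked primary outcomes, each with three arm comparisons, make nine primary tests with no visible error control, and the HIV-positivity outcome has very low power

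*Protocol article*

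**What the plan says.** The Outcomes section lists three primary outcomes with no ranking: "The primary outcomes of this trial consist of three parts: 1) Mean number of motivated alters who have photo-verified self-testing per index in each arm", the proportion of alters testing for the first time, and "Proportion of alters with a positive HIV testing result in each arm". The Measures section again treats all three as primary.

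The Primary analysis section fixes the tests and contrasts: "we will compare calculated means using two-sample t-test, and proportions using chi-square between SD/monetary incentives arm and control arm", then "SD/monetary incentives plus peer referral arm and control arm, and also between two intervention arms". Each outcome therefore gets three pairwise tests.

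The Sample size section gives the only significance level and uses only the mean number of alters per index: 0.65, 1.0 and 1.4, with a common SD of 0.5. The result is 300 indexes (100 per arm) "with a power of 0.90, an alpha of 0.05, and a lost to follow-up rate of 0.20".

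The three hypotheses concern the number of kits an index distributes. None mentions first-time testing or HIV positivity. The article gives no expected HIV positivity for alters. The nearest figure is for the local population: Zhuhai "has approximately 17,000 MSM with an HIV prevalence rate of 7" (per cent).

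**The concern.** Three outcomes times three arm pairs gives nine tests under the heading of the primary analysis. Nothing in the article says which test carries the trial, how many must succeed, or how the 0.05 is shared. Any one of nine significant results could then be reported as a positive primary finding, and the 5% error rate would apply to none of those claims taken as a set.

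The three outcomes are also unequal in information. The first was sized. The third counts a rare event in a few hundred alters at most, yet it has the same rank. A non-significant result on it would say little about whether the interventions change positivity among alters. A significant one would come from a small number of events.

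**Working it through.** **1. The plan's own sample size.** Inputs (Sample size section): smallest difference 1.0 − 0.65 = 0.35, SD 0.5, alpha 0.05 (two-sided assumed, since the side is not stated), power 0.90, loss 0.20.

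n per arm = 2 × (1.960 + 1.282)² × 0.5² / 0.35² = 42.9, so 43. After loss, 43 / 0.80 = 53.75, so 54 per arm and 162 in total. The stated 300 is not reproduced; it exceeds what its inputs require. Power for the 0.35 difference is 0.993 with 80 evaluable per arm and 0.999 with 100.

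**2. Familywise error under the global null, each test at 0.05 two-sided.**
- One outcome: the three pairwise z-statistics share arms and so are correlated. The chance that at least one exceeds 1.96 in absolute value, by simulation with 2 million draws, is 0.122.
- Three outcomes taken as independent: 1 − (1 − 0.122)³ = 0.32.
- Only the two proportion outcomes null: 1 − (1 − 0.122)² = 0.23.
- For reference, nine fully independent tests: 1 − 0.95⁹ = 0.37.

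Using the discrete, uncorrected chi-square for HIV positivity leaves the overall figure at 0.32 to 0.33. With continuity correction it is 0.27 to 0.28.

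**3. Expected HIV-positive alters.** Formula: indexes × mean alters per index × positivity. The 7% is an assumption carried over from Zhuhai MSM, so a range is shown.

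| Indexes per arm | Alters (control / incentives / incentives plus referral) | 5% | 7% | 10% |
|---|---|---|---|---|
| 100 | 65 / 100 / 140 | 3.3 / 5.0 / 7.0 | 4.6 / 7.0 / 9.8 | 6.5 / 10 / 14 |
| 80 | 52 / 80 / 112 | 2.6 / 4.0 / 5.6 | 3.6 / 5.6 / 7.8 | 5.2 / 8.0 / 11.2 |

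**4. Chi-square on HIV positivity, by exact enumeration of the two binomials.**
- Size at 7% in both arms: 0.049 to 0.056 across the three pairs, at 80 and at 100 indexes per arm.
- Power for 7% vs 14% against control: 0.27 to 0.29 with 100 indexes per arm, 0.22 to 0.23 with 80.
- Power for 7% vs 14% between the intervention arms: 0.39 with 100, 0.31 with 80.

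These figures treat alters as independent. Positive clustering of alters within an index would lower the power further.

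**5. Can the sized outcome bear adjustment?** Smallest difference 0.35, SD 0.5, power 0.90:

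| Adjustment | Alpha per test | Per arm | After 20% loss | Total | Power with 80 per arm |
|---|---|---|---|---|---|
| Bonferroni over 3 | 0.0167 | 56 | 70 | 210 | 0.98 |
| Bonferroni over 9 | 0.0056 | 68 | 85 | 255 | 0.95 |

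Both totals are below the planned 300.

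**The case against.** The strongest objection is that much of this is an absence. The article gives "an alpha of 0.05" only as a sample-size input and never says that each test will be run at that level. Multiplicity is often settled in an analysis plan, and that document is not at hand. This stands as a limit on the claim. What the article itself fixes is three unranked primaries and three prescribed tests on each, with a sample size built on only one of them.

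Four stronger readings are tempting, and the document does not support them.

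- *A flat one-in-three chance of a false primary claim.* The 0.32 needs all nine nulls true, outcomes roughly independent, each test at 0.05, and any single success counting. The article states no success rule. If all three outcomes had to succeed, this inflation would vanish, but the weak third outcome would then largely decide the trial.
- *An invalid chi-square because an expected count is below 5.* At 7% this happens only in the two comparisons with control, narrowly at full enrolment (65 × 0.07 = 4.55), and at 10% not at all. The test's size stays close to 0.05. The defect is power.
- *7% as the protocol's figure for alters.* It describes MSM in Zhuhai, whereas the control-arm description allows alters to be sexual partners or friends.
- *The three hypotheses as statements of the first primary outcome.* They concern kits distributed; the outcome counts alters with photo-verified tests. The case for putting that outcome first rests on the sample size alone.

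It is also fair to say that the Background and Objectives sections name first-time testers and positive cases as aims. Demoting those outcomes is therefore partly a judgement about purpose, and adjusting over all nine tests is a legitimate alternative.

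**Conclusion.** The concern holds in a conditional form. The article sets nine primary tests and shows one alpha of 0.05, without an order, adjustment or success rule. Followed as written, with any significant result counting, it does not hold familywise error at 5%: about 0.12 within one outcome and about 0.32 over three independent outcomes under the global null. Even if the first outcome has a real effect, the two proportion outcomes leave about 0.23 if both are null. An analysis plan not shown could already resolve this.

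HIV positivity is severely underpowered for a primary outcome. At an assumed 7%, a doubling would be missed about 61% to 78% of the time (1 − 0.39 to 1 − 0.22), before clustering. This rests on the protocol's alter means and on the assumed positivity.

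The conclusion that the first outcome can bear adjustment depends on the SD of 0.5. For an integer count with mean 0.65 the smallest possible SD is √(0.65 × 0.35) = 0.477, so 0.5 is optimistic. With an SD of 0.9, power for the 0.35 difference at 0.0056 and 80 per arm would be about 0.38.

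**What to change.** State the error control in the protocol or analysis plan before any analysis. The Trial status section says analysis has not begun, so the change can still be prespecified.

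**Preferred.** Place the mean number of alters with photo-verified testing first, because it is the outcome used for sizing. Test it by a closed procedure: a three-arm global test at 0.05, then each pairwise test at 0.05 only if the global test is significant. With exactly three arms this controls familywise error for that outcome without splitting alpha. Test first-time testing and HIV positivity afterwards in a stated order, or make them key secondary outcomes. If they stay in the confirmatory sequence, write down the condition for moving on. In a strict fixed order, that means all three comparisons on the preceding outcome are significant. Report HIV positivity mainly as estimates with confidence intervals.

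**Alternative.** Keep all three as primary and apply Holm or Bonferroni over the nine tests. On the protocol's inputs with 80 evaluable per arm, the first outcome keeps power of about 0.95 for the 0.35 difference. HIV positivity becomes weaker still.

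**Cost.** Wording and a registry update, with no change in sample size on the protocol's inputs. There would be fewer claims from the second and third outcomes and, under the closed procedure, no pairwise claim on the first if its global test fails.

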Digital health is also considered to be an innovative strategy to deal with traditional health challenges, including challenges for HIV prevention [17]. For example, digital health has been used to promote safe sex, condom use, and awareness of HIV or sexually transmitted diseases among key populations [18, 19]. For MSM, social networking or dating apps are widely used, especially among young MSM, which provides a unique opportunity of leveraging digital health in improving health services among them. Combining digital health and social network-based strategy for HIV testing (i.e., secondary distribution) promotion can help surpass traditional barriers and reach more people who have never been reached by the facility-based services and increase case finding.

In this study, we intend to examine two modified secondary distribution approaches for HIVST through a three-arm randomized controlled trial in Zhuhai, China. The main purpose of this study is to compare the effectiveness of two modified secondary distribution approaches (monetary incentives, and monetary incentives plus peer referral) with the traditional secondary distribution approach, in order to determine whether these two approaches can increase the uptake of HIVST among MSM, especially the first-time testers among alters.

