## Objectives

Our trial aims to enable more Chinese MSM to receive HIV self-testing, reach more first-time HIV testing alters, and identify more people with an HIV-positive (reactive) result by implementing the photo-verified HIV self-testing method under different scenarios, i.e., standard secondary distribution, secondary distribution with monetary incentives and secondary distribution with monetary incentives plus peer-referral links.

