### Measures

In general, we aim to examine the effectiveness of our modified secondary distribution models. Primary outcomes of this trial are the number of alters, first-time testing alters, and HIV-positive alters in each arm, therefore, all testers’ information will be specifically clarified and recorded. All data will be collected through JINSHUJU, a secure online platform where participants can apply for HIVST kits, report testing results, and complete the baseline and follow-up questionnaires. All data collected from participants will be examined and deduplicated according to phone number and IP.

In the baseline survey, we will collect the socio-demographic characteristics, sexual orientation, sexual behavior, HIV testing history, and social network. When alters return the results, they will also complete a questionnaire online. In this survey, except for basic information on socio-demographic characteristics, sexual orientation, sexual behavior, HIV testing history, and social network will be collected. We will also investigate the attitudes and experiences towards self-test. The follow-up survey for indexes will take place 3 months after the application completed, which focuses on experiences and attitudes on using and distributing self-test kits. The survey mainly inquires about the occurrence of intimate partner violence (IPV) or other adverse events, the relationship between the indexes and the alters, whether indexes have tested together with the alters, and whether indexes have guided the alters on how to perform HIVST.

Specifically, in our surveys, socio-demographic characteristics include indexes’ age, sex, marital status, the highest level of education completed, and monthly income level. Sexual behavior within 3 months includes previous sex with males and females, role during sex with males, condom use, number of sex partners, and drug use. HIV testing history includes health care facility-based and online HIV testing experience. Social network collects community engagements [7], community connectedness [20], identity fusion [21], and social cohesion [22].

All blood samples will be analyzed using *SD Bioline* HIV/Syphilis duo test kits (*SD Bioline Company*, South Korea). Participants will collect fingertip blood samples by themselves according to the instruction. The trained staff of the CDC or CBO will check and read the photos of result and record them in JINSHUJU. The results are subject to the reading of the staff.

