### Data analysis

All statistical analyses will follow the intention-to-treat principle. Missing data will be handled by multiple imputations. Categorical variables from the baseline survey will be aggregated in frequency distributions, and numerical variables will be summarized in mean and standard deviation.

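### Primary outcomes 2 and 3 are tested as proportions among alters who tested, although the Measures section calls them numbers and the objectives ask whether more people are reached

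*Protocol article*

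**What the plan says.** The protocol describes these outcomes in two ways.

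**As proportions.** In the Outcomes section, outcome 1 is a count per index: "1) Mean number of motivated alters who have photo-verified self-testing per index in each arm". Outcomes 2 and 3 are shares of alters: "2) Proportion of first-time HIV testing among alters in each arm; 3) Proportion of alters with a positive HIV testing result in each arm". The Primary analysis section keeps this form, listing "mean number of alters that each index recruited, proportion of first-time HIV testers, and proportion of alter testers with an HIV-positive result", and states that "we will compare calculated means using two-sample t-test, and proportions using chi-square" for each pair of arms.

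**As numbers.** The Measures section says "Primary outcomes of this trial are the number of alters, first-time testing alters, and HIV-positive alters in each arm". The Objectives are to "reach more first-time HIV testing alters, and identify more people with an HIV-positive (reactive) result". The Background gives the main purpose as finding out whether the two approaches can "increase the uptake of HIVST among MSM, especially the first-time testers among alters".

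The Data analysis section adds that "All statistical analyses will follow the intention-to-treat principle". Only indexes are randomised (Trial design; Allocation). No section reconciles the two definitions.

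**The concern.** How many first-time testers an arm produces and what share of its alters are first-time testers are different quantities, and they need not move together. The interventions are meant to increase the number of alters who test, which is the denominator of outcomes 2 and 3. The proportion therefore divides out much of the effect that the objectives describe.

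It also compares sets of alters that formed after randomisation, and an index who brings in no alter contributes nothing to it.

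Two of three primary outcomes could then report no difference, or point the wrong way, when the objective has been met. While both definitions stand, the choice between number and proportion could also be made after the results are known.

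**Working it through.** **Inputs**
- Expected alters per index (Sample size, from preliminary data): 0.65 control, 1.0 incentives, 1.4 incentives plus referral.
- Indexes per arm (Sample size): 100.
- First-time share among alters: not given. Assumed 40% in control, with 20% to 50% as the range.
- HIV-positive share among alters: not given. Assumed 7% in every arm, borrowed from the prevalence among local MSM in the Study setting section.

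The plan gives no figure for outcomes 2 and 3 to reproduce; its sample size rests on outcome 1 alone.

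**1. Expected denominators.** Alters = indexes × mean: 65, 100 and 140. The largest ratio is 1.4 / 0.65 = 2.15. For a count, the fraction of indexes with at least one alter cannot exceed the mean. So at a control mean of 0.65, at least 35% of control indexes have no alter and are absent from outcomes 2 and 3.

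**2. Equal shares.** First-time testers = alters × share.
- Control: 65 × 0.40 = 26, or 0.26 per index.
- Incentives plus referral: 140 × 0.40 = 56, or 0.56 per index.
- Ratio: 56 / 26 = 2.15.
- Planned test, 26/65 vs 56/140: 40% vs 40%, chi-square 0, p = 1.0.
- Simple Poisson comparison of 26 with 56 over equal numbers of indexes: p about 0.001.

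The ratio of 2.15 holds for any common share; 40% only sets the counts. The Poisson p-value ignores extra variation between indexes, so a robust analysis could give a larger one.

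For outcome 3 at 7% in every arm, the expected positives are 65 × 0.07 = 4.6, 100 × 0.07 = 7 and 140 × 0.07 = 9.8. Outcome 3 again shows no difference.

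**3. Unequal shares.** Let r be the intervention share divided by the control share. The intervention arm finds more first-time testers when r exceeds the control mean divided by the intervention mean:
- Incentives: r > 0.65 / 1.0 = 0.65.
- Incentives plus referral: r > 0.65 / 1.4 = 0.464.

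Between that threshold and r = 1, the count favours the intervention and the proportion favours control.

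**4. Can the reversal be significant?** Incentives plus referral vs control, 100 indexes per arm:

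| Control share | r | First-time testers, control vs intervention | Chi-square p |
|---|---|---|---|
| 40% | 0.75 | 26/65 vs 42/140 | 0.157 |
| 40% | 0.70 | 26/65 vs 39/140 | 0.08 |
| 40% | 0.60 | 26/65 vs 34/140 | 0.021 |
| 50% | 0.60 | 32/65 vs 42/140 | 0.008 |
| 30% | 0.60 | 20/65 vs 25/140 | 0.038 |
| 20% | 0.60 | 13/65 vs 17/140 | 0.14 |

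Counts are rounded to whole persons. At a 40% control share, unrounded, p is 0.043 at r = 0.65 and 0.086 at r = 0.70. A significant reversal there needs r of about 0.65 or lower.

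**The case against.** **Total yield is already covered.** Outcome 1 counts tested alters per index, and all three hypotheses concern the quantity of kits distributed. First-time testers per index equals outcome 1 times outcome 2, so it can be worked out from what will be reported. This stands, and it limits the severity. But that product is not itself tested, and it is the quantity that the Objectives single out.

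**The reversal rests on assumed shares.** This also stands. A reader might infer that an intervention arm would be declared worse. The documents do not support that. They give no first-time share in any arm, a moderate fall (40% to 30%) gives p = 0.157, and the protocol sets no success rule from which a trial-level verdict would follow. Nor are 0.65, 1.0 and 1.4 features of the design; they are expectations from preliminary data. The equal-share result is firmer, because it needs no difference in shares.

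**The remedy does not guarantee significance.** True. As simple Poisson counts, 26 vs 42 gives p of about 0.055, 26 vs 34 gives 0.30, and 4.6 vs 9.8 positives gives about 0.18. The change corrects what is estimated; it does not make small differences detectable.

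**Intention-to-treat.** A reader might say the proportions breach this principle outright. Alters can still be grouped by their index's allocated arm, so the accurate statement is that the comparison is conditional on recruitment.

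**The proportions are informative.** They describe who is reached, which the Discussion in the abstract cares about. That is a reason to report them, not to let them stand in for yield.

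**Conclusion.** The contradiction is in the current text. The Outcomes and Primary analysis sections use proportions; the Measures section uses numbers, and the Objectives and Background ask for more people reached. Followed as written, the plan tests a quantity that does not measure the stated objective for two of its three primary outcomes.

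Given the protocol's expected means and any equal first-time share, a 2.15-fold difference in first-time testers shows as no difference on outcome 2. A reversal of direction is possible over a wide range of shares, but whether it would be significant cannot be told from the document.

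This should be fixed before analysis. It does not undermine outcome 1 or the three hypotheses.

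**What to change.** By a dated, justified amendment before analysis starts:
- Define primary outcome 2 as the number of first-time-testing alters per randomised index, and primary outcome 3 as the number of HIV-reactive alters per randomised index, with zero where there are none.
- Compare arms at index level over all randomised indexes, by difference in means or by rate ratio with robust standard errors.
- Report the proportions among alters as secondary results on who is reached, and state that they are conditional on recruitment.
- Align the Outcomes, Measures and Primary analysis sections.

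The data are already being collected. The Trial status section says that analysis has not begun but enrolment is under way, so this is a mid-trial change to primary outcomes and the registry entry must be brought into line. The proportions lose primary status, and precision for HIV-reactive alters will stay low because few are expected.
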